## Abstract

**Background:**

There is an increased risk of transmission of sexually transmitted infections (STIs), including HIV, in the postoperative period after receiving voluntary medical male circumcision (VMMC). In South Africa, over 4 million men are being targeted with VMMC services but the health system is not able to offer quality counseling. More innovative strategies for communicating with and altering behavior in men and their partners in the postoperative period after VMMC are needed.

**Objective:**

This paper presents a study protocol to test the effectiveness of an mHealth intervention designed to task-shift behavior change communication from health care personnel to an automated phone message system, encouraging self-care.

**Methods:**

A single-blind, randomized controlled trial will be used. A total of 1188 participants will be recruited by nurses or clinicians at clinics in the study districts that have a high turnover of VMMC clients. The population will consist of men aged 18 years and older who indicate at the precounseling session that they possess a mobile phone and consent to participating in the study. Consenting participants will be randomized into either the control or intervention arm before undergoing VMMC. The control arm will receive the standard of care (pre- and postcounseling). The intervention arm will received standard of care and will be sent 38 messages over the 6-week recovery period. Patients will be followed up after 42 days. The primary outcome is self-reported sexual intercourse during the recovery period. Secondary outcomes include nonpenetrative sexual activity, STI symptoms, and perceived risk of acquiring HIV. Analysis will be by intention-to-treat.

**Results:**

Enrollment is completed. Follow-up is ongoing. Loss to follow-up is under 10%. No interim analyses have been conducted.

**Conclusions:**

The intervention has the potential of reducing risky sexual behavior after VMMC. The platform itself can be used for many other areas of health that require task shifting to patients for better efficiency and access.

**Trial Registration:**

Pan-African Clinical Trial Registry: PACTR201506001182385

## Introduction

### Background

Voluntary medical male circumcision (VMMC) has been shown to reduce risk of male acquisition of HIV by as much as 60% [1-3]. Based on this evidence, in 2007 the World Health Organization (WHO) and the Joint United Nations Programme on HIV/AIDS (UNAIDS) stated that “male circumcision should now be recognized as an efficacious intervention for HIV prevention” and that male circumcision should be promoted as an additional strategy in the prevention of HIV in men [4]. Thirteen countries in eastern and southern Africa with high HIV prevalence and low rates of male circumcision were prioritized for VMMC scale-up [5]. Significant technical and financial resources were provided by various funding and technical agencies, and the governments of these countries began a process of conducting situation analyses, drafting policies and protocols, and rolling out VMMC [5]. As a result of these efforts, by the middle of 2014 over 5.8 million VMMCs had been performed, more than half of which occurred in 2013 [6].

### Early Resumption of Sexual Intercourse After VMMC

Expert guidelines for VMMC recommend a 6-week period of abstinence from penetrative sex after VMMC in order to avoid the spread of sexually transmitted infections, including HIV [7]. The risk of early resumption of sex exists without proper counseling, education, and follow-up. In the Rakai, Uganda trial, about 11% of HIV-positive and HIV-negative participants reported having intercourse before certified wound healing, defined in this study as “when there was an intact healthy scar with no residual exudate or scab formation, and all sutures had been completely absorbed” [8]. Married men were more likely to resume sexual intercourse before certified wound healing whether or not they were HIV positive (28%) or HIV negative (29%). This was despite intensive pre- and post-VMMC counseling within the trial, indicating strong sociocultural desire for quick resumption of marital sexual relations. In the same study, it was observed that more female HIV-negative partners of HIV-positive VMMC recipients enrolled in the trial acquired HIV when the couple resumed sex early (more than 5 days prior to certified wound healing) as opposed to those who did not [9]. In an observational study more approximating realistic clinical VMMC situations in Nyanza, Kenya, 30.7% of all participants resumed sexual intercourse before wound healing, usually in the first 3 to 4 weeks after VMMC [10]. Again, being married or cohabiting was the strongest predictor of having early sex: 65.7% of married participants resumed sex before healing despite counseling efforts by clinicians. Finally, a recent study from Zambia found that 24% of circumcised men resumed sex early, nearly half of whom (46%) did so in the first 3 weeks [11].

Cultural norms play an important role in expectations surrounding sexuality, and this has implications for health education messaging. Qualitative research from Nyanza, Kenya, indicates that the postoperative abstinence period is spontaneously cited by uncircumcised men as a barrier to obtaining VMMC; in particular, the 6-week period was considered too long to abstain [12]. Younger men were worried that their female partners would seek sex elsewhere, while older men worried that it would not be possible to sleep in the same bed as their wives and abstain. In the formative phase of the current project, we used qualitative methods to understand how newly circumcised men and their female partners feel about the 6-week abstinence period after VMMC. Our results confirm that it is not always easy for couples to navigate this period [13]. They live in close quarters so cannot avoid sleeping in the same bed, alcohol (and drug) use sometimes impairs their judgment, and there are expectations of sexual activity among married couples that men say they feel obliged to live up to.

### Pre- and Postoperative Counseling and Education

All of the studies above have reiterated the need for proper counseling and education about the efficacy of VMMC and the need to maintain or adopt proper risk avoidance behavior after the procedure, particularly during the healing period. In the Rakai, Uganda, trial the authors concluded that “the association between resumption of sexual intercourse before complete wound healing and increased risk of male-to-female HIV transmission makes it imperative that circumcised men and their female partners are clearly instructed to abstain from intercourse until the wound is healed” [9]. In a pooled analysis of the three original efficacy trials, Mehta et al (2009) found that men reporting early sex did not have increased risk for HIV after 3 or 6 months [14]. However, the authors acknowledged that the intensive counseling involved in the context of the three studies is not likely to be replicated in real life, indicating the importance of continued vigilance regarding actual counseling practices and resulting behaviors. Further, more intensive counseling of married men, due to their increased likelihood of resuming sex early, was recommended by the authors.

A recent study indicated the effectiveness of a 180-minute theory-based risk reduction group counseling session in reducing sexual risk behavior following VMMC, although the study did not report on early resumption of sex [15]. This is a promising intervention for informing VMMC programs. However, there is also recognition that the lack of human resources in the VMMC scale-up countries presents a barrier to such intense services, particularly if repeated messaging is to occur [16]. This is particularly the case when countries turn to independent partners to carry out mass, one-off VMMC campaigns outside of the normal constellation of services. Clearly, more innovative strategies for communicating with and effectively altering behavior in men and their partners are needed. Further, given evidence of greater risk for resumption of sexual activity in married/cohabiting men, strategies for nonpenetrative sexual activity should be developed and included in such education.

### mHealth As a Self-Care Strategy

Mobile health (mHealth)—the use of mobile phone technology to deliver health care—has emerged as an important and appreciated complement to health care education delivered through traditional channels. Such technology may include the use of text messaging, video messaging, voice calling, and Internet connectivity. The potential for mHealth interventions to partially compensate for interpersonal services in resource-poor areas is enormous [17]. Although mHealth has been shown to be effective in medication adherence, clinical management, and behavior modification [18], the use of mHealth has primarily been restricted to developed countries. To date, there are few studies of the use of voice messages to reduce risky sexual behaviors. In fact, a Cochrane Review from 2013 found only one RCT of a telephone-delivered intervention (use of postexposure prophylaxis for rape victims) for preventing HIV infection in HIV-negative persons [19]. Further, most mHealth interventions are not theory-based, leading to poor results [20].

### South Africa

South Africa holds the dubious title of being the country with the highest number of HIV positive individuals – over 6 million – and it accounts for 16% of all new HIV infections in the world [21]. Based on antenatal data, HIV prevalence in the general population is estimated at 17.3% in South Africa [22], with incidence estimated at 1.43%. Transmission of HIV in South Africa is almost exclusively through heterosexual sex, thus heightening the importance of VMMC as a form of prevention [23].

South Africa has committed to rolling out medical circumcision as one source of protection from HIV [24]. Circumcision is available as part of a comprehensive service at district hospitals, and, in theory, HIV testing, counseling, and HIV education are provided before the procedure. However, the South African health system is struggling to maintain high-quality counseling services around male circumcision due to human resource issues [5].

The Coloured community, which accounts for 48.8% of the Western Cape’s population [25], has a growing HIV prevalence rate—7.5% according to 2012 antenatal data [22]. The heightened HIV risk to this population group lies at least partly in high illicit drug and alcohol use, which is associated with risky sexual behavior [26].

Mobile phone ownership in South Africa is nearly universal—97% of households have a mobile phone, with greater concentrations of ownership in the urban centers. Particularly within the urban setting there is little difference by income level in terms of access to phones [27]. Given this near-universal ownership, mobile phone technology has been found to be acceptable and feasible for HIV- and AIDS-related prevention and services [28,29] and is now used in several health-related text-reminder projects in South Africa [30].

### Objectives

The objective of this study was to test the effectiveness of a customized relay of audio clips on safe sexual behavior in consenting, recently circumcised men.

## Methods

### Overview

The study is a randomized controlled trial (RCT) with two arms. The control arm consists of standard of care for pre- and postoperative counseling offered to VMMC recipients by the South African Department of Health VMMC services. In the intervention arm, VMMC recipients will receive voice messages for 6 weeks following the operation in addition to the standard of care. Data collection began January 21, 2015, and is ongoing.

### Study Setting and Participants

The research will be done in seven clinics in Cape Town, in the Western Cape Province of South Africa. The study sites were chosen in conjunction with the provincial health department. The communities in each of the seven catchment areas are almost exclusively Afrikaans-speaking Coloured. The term Coloured refers to an official South African race group used in research and census data that is predominantly mixed ancestry. The term originated in the apartheid era but remains an important descriptor and label for a distinct community. More than 48% of the people who live in the Western Cape are classified as Coloured, mostly still living in defined communities that are at least 90% Coloured. Inclusion criteria are men aged 18 years and older who present for VMMC at one of the study clinics and indicate at the precounseling session that they possess a mobile phone and consent to participate in the study. There are no exclusion criteria.

### Standard of Care (Control Group)

The standard of care offered by the provincial circumcision team consists of the counseling session during the HIV testing and counseling procedure and a brief postsurgery counseling session where men are advised on how to care for the wound and ordered to go to their local clinic at 2 days and 7 days following surgery. They are reminded not to engage in penetrative sex until the mandatory wound-healing period of 6 weeks has passed. No further contact is sought other than if there are health complications such as swelling or infection.

### Intervention Group

The intervention group gets the standard of care plus the intervention program which consists of 38 audio messages delivered over the 42 days following surgery. Once men are randomized into the intervention group, the project manager passes on the participants’ mobile phone numbers, personal identification numbers, and dates of enrollment to the mHealth platform operator (the South African company Health Information Systems Program [HISP]). The mobile system will automatically call participants twice a day for the first 2 days, once a day for the next 4 weeks, and on alternative days in the last 2 weeks. Using the last 4 digits of their mobile number as their password, participants can listen to the message and, using their keypad, replay it if they do not understand the message. It is not possible to respond to the message. The platform is programmed to redial unanswered or busy numbers up to 3 times. Therefore, calls can be received at different times of the day.

The content and phasing of the messages for the mHealth intervention were developed collaboratively with former patients through focus group interviews, cognitive interviews, and discussions with health promotion experts at the Provincial Medical Office (research to be published separately) using classic behavior change theories. The messages were then developed into short audio clips of 30 to 120 seconds each (in English and Afrikaans). Based on the formative research, messages delivered over the 42 days are divided into four periods:

Days 1-2: An intense 2 days of self-care messages (2 per day). The theme of these messages revolves around coping with pain and recuperation.Days 3-14: Mainly self-care messages (1 per day). The theme is around strategies and practical tips on pain and wound management.Days 15-28: Coping and inspirational messages (1 per day). The theme is around coping with the wound inspiring and encouraging them to include their partners into the recovery period.Days 29-42: Inspirational messages (triweekly). The theme is around offering alternatives to penetrative sex and inspiring them to complete the period penile penetration-free.

### Outcomes

The primary outcome is occurrence of sexual intercourse (vaginal or anal) at any time in the 42 days after the procedure. Secondary outcomes include (1) adoption of nonpenetrative sexual behaviors in the first 42 days after the procedure, (2) self-reported sexually transmitted infection symptoms at baseline and 42 days after the procedure (as a marker of unprotected sex), (3) sexual risk behavior at baseline and 42 days after the procedure, and (4) sexual risk propensity at baseline (as a control for risk-taking personality) [9].

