### Data Collection

Data is collected through self-administered paper and pen questionnaires offered in either English or Afrikaans. The consenting participants fill out the questionnaire while they wait for their HIV testing and preoperative counseling. They are asked to come back to the clinic for a follow-up visit after 6 weeks. HIV status will be collected (coded) from files if consent is given by the participant. Completed questionnaires are processed and captured at the office by the data capturer and stored in a locked room. The completed questionnaires are linked to the participants through their study numbers only and not the electronic health platform.

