### Analysis

#### Descriptive Analysis

Data will be analyzed using Stata 13 statistical software (StataCorp LP) according to the intention-to-treat principle. Descriptive statistics will be used to summarize the data. Continuous outcome variables will be tested for normality using descriptive statistics (eg, histograms, qq plots, and box plots). If normally distributed, continuous variables will be presented as means and standard deviations; if not, they will be reported as medians and interquartile ranges. Categorical data will be presented as proportions. An alpha of .05 will be considered statistically significant, and 95% confidence intervals will be reported where appropriate. Baseline prognostic variables and possible confounders will be compared between intervention and control groups using the appropriate univariate statistical methods. Clinical imbalances will be considered in further adjustment regression models.

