#### Inferential Analysis

The primary outcome—occurrence of any homosexual or heterosexual penetrative intercourse at any time in the first 42 days after VMMC—will be compared between the intervention and control groups. The primary analysis will be to detect a difference in proportions using an unadjusted binomial test. Additionally, generalized linear regression models for the analysis of binary outcomes will be used to study the effects of the intervention as well as possible synergistic effects, taking potential confounders into account if necessary (eg, age, religion, marital status, education, employment, depression). The final covariate model will include all variables known to have a meaningful impact on bias in the estimate of the treatment effect. The covariate adjusted relative risk for treatment effect and 95% confidence interval will be reported. A covariate adjusted absolute risk difference for the effect of treatment and the 95% confidence interval will also be presented. In addition, we will report number needed to treat.

Secondary outcomes will be analyzed in the same manner as the primary outcome. A per-protocol compared to intention-to-treat sensitivity analysis will be performed on the primary outcome.

Missing primary outcomes will be assumed to be missing at random; however, if more than 15% of all primary outcomes that should be available for analysis are missing, a sensitivity analysis will be undertaken in addition to the primary missing at random analysis and results compared.

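### A baseline control variable is listed as a secondary outcome, two outcomes measured twice have no stated role for their baseline value, and the abstract names a secondary outcome that the Methods lack

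*Protocol article*

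**What the plan says.** The Outcomes section of the protocol article numbers four secondary outcomes.

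- The first is the adoption of nonpenetrative sexual behaviours over the 42 days.
- The second is "self-reported sexually transmitted infection symptoms at baseline and 42 days after the procedure (as a marker of unprotected sex").
- The third is given as "3) sexual risk behavior at baseline and 42 days after the procedure".
- The fourth is given as "4) sexual risk propensity at baseline (as a control for risk-taking personality").

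The Inferential Analysis section compares the primary outcome between arms with an unadjusted binomial test. It then plans additional generalized linear models with covariates if needed, and an adjusted relative risk and risk difference. Its example covariates are age, religion, marital status, education, employment and depression. For the rest it states: "Secondary outcomes will be analyzed in the same manner as the primary outcome". No exception is made for the fourth item.

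The abstract gives a different list: "Secondary outcomes include nonpenetrative sexual activity, STI symptoms, and perceived risk of acquiring HIV".

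On timing, the Data Collection section says: "The consenting participants fill out the questionnaire while they wait for their HIV testing and preoperative counseling". According to the Blinding section, intervention participants are registered after the recruitment day and begin to receive messages the following day.

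**The concern.** An outcome must be something the intervention could change. Risk propensity at baseline is fixed before the first message, so a comparison between arms can show only chance imbalance. Followed literally, the analysis rule would still produce a treatment effect and a p-value for it. The one variable that the article calls a control is also missing from the example covariates.

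STI symptoms and sexual risk behaviour are each defined at two time points. The article does not say whether the target is the day-42 value, the change, or new occurrence, and it gives the baseline value no role. Information that is already collected may go unused.

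Perceived risk of acquiring HIV is an outcome in the abstract and absent from the Methods. A reader of the final report could not tell whether it was prespecified, which leaves room to choose the reported set after the data are seen.

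**Working it through.** **The plan's own figure.** The article states no figure for any secondary outcome. Its one relevant number is the sample size of 594 per arm (60% against 50%, 90% power, alpha 0.05, taken as two-sided). The normal formula gives 519 per arm, and 519/0.9 = 577. With continuity correction it gives 538, and 538/0.9 = 598 or 538 × 1.1 = 592. The stated figure is therefore reproduced to within 3%, and 540 × 1.1 = 594 exactly. I use 540 evaluable per arm below. Nothing in this point changes the sample size.

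**Item 4.** Two sections fix the order of events. The questionnaire is completed in the waiting period before HIV testing and preoperative counselling (Data Collection). Messages begin the day after recruitment (Blinding). The effect of the messages on the item is therefore zero. If answers do not depend on allocation, a test at alpha 0.05 rejects with probability of about 0.05 whatever the messages do.

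**Items 2 and 3: validity.** Randomisation makes a day-42 comparison valid without baseline adjustment. As a check, take a binary outcome with an assumed 20% event rate in both arms and 540 per arm. A simulation of 5,000 null trials with a pooled two-proportion z test rejected in 5.6%, with a Monte Carlo standard error of about 0.3 points. Exact enumeration of the same test gives 5.0%, so the small excess in the simulation is noise.

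**Items 2 and 3: precision.** For a continuous score with baseline to day-42 correlation r, the variance of the baseline-adjusted comparison relative to the day-42-only comparison is 1 − r². To express this as power, take the standardised effect that gives 80% power without the baseline:

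d = (1.96 + 0.84) × √(2/540) = 0.17 SD.

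Power after adjustment is Φ(2.80/√(1 − r²) − 1.96).

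| Assumed r | 1 − r² | Variance reduction | Power |
|---|---|---|---|
| 0.2 | 0.96 | 4% | 82% |
| 0.3 | 0.91 | 9% | 84% |
| 0.5 | 0.75 | 25% | 90% |
| 0.6 | 0.64 | 36% | 94% |

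The article gives no r and no scale for either item. The formula is for a linear model and does not carry over directly to a yes/no item.

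**The two lists side by side.**

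| Secondary outcome | Abstract | Outcomes section |
|---|---|---|
| Nonpenetrative sexual activity | yes | yes |
| STI symptoms | yes | yes |
| Perceived risk of acquiring HIV | yes | no |
| Sexual risk behaviour | no | yes |
| Sexual risk propensity at baseline | no | yes |

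**The case against.** The strongest reply is that this is a labelling slip. The bracketed words state the purpose of the fourth item, and a sensible analyst would not test it. That is probably so. But the same-manner rule has no exception and the example covariates omit the item, so the text gives it the wrong role and does not name it in the right one.

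A reader might infer that the secondary analyses are invalid. The article does not support this. Only a test of item 4 would be uninformative. Day-42 comparisons of the second and third outcomes are valid under randomisation, and the first is untouched.

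A reader might also infer that the baseline values are excluded. They are not. The same-manner rule also carries over the additional regression models, their covariate list is open, and the Descriptive Analysis section allows adjustment for imbalance. The role of the baseline is simply not fixed, and a fuller plan that is not shown may fix it.

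Nor can the binomial test be called the wrong test. The sentence "Continuous outcome variables will be tested for normality using descriptive statistics" is a general descriptive rule and assigns no scale to the second or third outcome. If both are yes/no, a comparison of proportions fits.

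It is also tempting to call item 4 a pre-randomisation measurement. The abstract says only: "Consenting participants will be randomized into either the control or intervention arm before undergoing VMMC". Study numbers are allocated in the waiting area, where the questionnaire is also completed, and the order of the two is not stated. Measurement before the intervention is clear, and that is enough for this point.

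Finally, both outcome lists are introduced as non-exhaustive, and an abstract may leave items out. That explains the two omissions. It does not explain an outcome that the Methods lack.

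**Conclusion.** The point holds in three limited parts.

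1. Sexual risk propensity at baseline is a covariate and cannot be an outcome. A test of it between arms would be significant about 5% of the time with no bearing on the messages. This assumes that allocation does not influence the answers.
2. For STI symptoms and sexual risk behaviour, the inherited lead test is valid but leaves the baseline unused. The possible cost is precision: about 4% to 36% of variance for a continuous score at an assumed correlation of 0.2 to 0.6. At the lower end this is negligible. Behaviour before surgery may correlate only weakly with behaviour during advised abstinence, so the lower end cannot be ruled out.
3. Perceived HIV risk is a true mismatch between the abstract and the Methods.

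The primary outcome, the sample size and the first secondary outcome are unaffected. The changes should be made, but they concern only the secondary analyses.

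**What to change.** Before unblinding:

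- Remove sexual risk propensity from the secondary outcomes and name it as a prespecified covariate in the adjusted models already planned. Leave the unadjusted primary test as it is.
- State that STI symptoms and sexual risk behaviour are analysed at day 42, adjusted for the same item at baseline. State each item's scale and use a model that suits it.
- Settle one secondary outcome list for the abstract, the Methods and the analysis plan, and say whether perceived risk of acquiring HIV is included.

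The cost is text edits only. The baseline questionnaire is already part of data collection, and no further participants or visits are needed. The article reports that follow-up is ongoing and that no interim analysis has been done, so as of that report the changes can still be made without sight of the results.
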